## Abstract

Road traffic injuries (RTIs) stands as one of the leading causes of mortality and morbidity across the globe. Effective injury surveillance systems and pre-hospital and in-hospital interventions set up in developing countries have shown promising results in controlling the problem. This study aimed to standardise and evaluate an evidence-based intervention for safety, efficacy and quality of post-crash pre-hospital and in-hospital trauma care services to improve the outcome in RTI victims. In addition, it establishes the android-based trauma registry for effective RTI surveillance.

This multi-centric, prospective, observational study is commissioned by the Indian Council of Medical Research (ICMR) as a National Task Force Project. This study is being conducted in five sites, viz., Anand, Bengaluru, Delhi, Lucknow and Thrissur located across India. Each centre will have a level I, two level II and three level III trauma hospitals. The study will be carried out in four phases namely: i) preparatory phase, ii) trauma registry establishment and pre-intervention data collection, iii) intervention and iv) impact evaluation. The preparatory phase, which lasts for four months includes the situational analysis pertaining to managing RTIs. Trauma registry will be initiated from the fifth month. Pre-intervention data will be collected for six months. The intervention will be conducted for six months in the form of prehospital notification, training for trauma care providers and trauma care quality improvement. Post-intervention data collection will continue for 12 months and the impact of the intervention will be assessed. The primary outcome measure will be early preventable mortality, defined as death at 24 hours after admission for patients with a calculated probability of survival >50% based on their injury severity score.

## Introduction

Road traffic injuries (RTIs) stands as one of the leading causes of mortality and morbidity across the globe. Approximately 1.24 million people die every year on the roads across the world, and another 20 to 50 million sustain non-fatal injuries as a result of RTIs. Eighty per cent of road traffic deaths occur in middle-income countries, which account for 72% of the world’s population but only with 52% of the world’s registered vehicles (1). The reasons for the high burden of RTIs in developing countries are - increasing in the number of motor vehicles, poor enforcement of traffic safety regulations, the inadequacy of health infrastructure and poor transport facilities (2).

In India, RTIs account for 15–50% of all injuries (3–5). Surveillance of RTIs is recommended to assess the burden, identify high-risk groups, establish an association with probable risk factors and plan interventions to control the occurrence and monitor impact (6). Effective RTI surveillance systems set up in developing countries have shown promising results in understanding the problem (7). It is the responsibility of the health system to ensure the establishment of necessary data systems including registries which will enable through the collection of information related to RTIs (8). However, systematic collection of road traffic data is not well developed in many developing countries including India and thus underreporting of injuries and deaths is common (9).

In the low and middle-income countries like India, injuries claim up to 18% deaths annually of which 50–60% of deaths occur either at the scene or en-route to the hospital (10). Faster response time and adequate prehospital care may dramatically improve these outcomes in critically injured patients (3). There is strong evidence to suggest that the establishment of an organized trauma system leads to improvement in patient outcomes, even in rural areas (4, 5). A recent prospective randomized study suggested that formal training in trauma care in the rural hospitals led to decreased length of time to transfer to appropriate hospitals as well as improved overall outcomes. It further demonstrated the cost-effectiveness and financial feasibility of such intervention in a rural setting (6). Timely and adequate care of a trauma patient is of utmost importance and it can dramatically impact the survival. There is a clear survival and functional benefit for critically injured patients to receive appropriate care within the first 60 minutes after injury. This concept is called the ‘Golden Hour’ (7, 11). The concepts of ‘pre-hospital care’ and ‘golden hour’ are still non-existent especially in the rural, remote and resource-poor regions (9). In this context, a study has been commissioned in five places in India by the Indian Council of Medical Research (ICMR) (12).

### Objectives of the study

The broad objective is to standardize structured evidence-based intervention for safety, efficacy and quality of post-crash pre-hospital and in-hospital trauma care services to improve the outcome in RTI victims. The specific objectives are (i) to study the prehospital trauma care system and emergency medical services (EMS) available in the district for identifying important components, which can improve the trauma health system in the district, (ii) to establish a prehospital care intervention through training of first responders and bystanders and sensitizing them about the importance of pre-hospital notification, (iii) to establish the intervention for emergency care by reorienting trauma care personnel and improving the facilities, (iv) to assess the overall impact of prehospital and in-hospital trauma care on the outcome of the RTI victims and (v) to establish a trauma registry system on electronic platform enabling data capturing through Android phones.

## Methods

### Study design and setting

This would be a multi-centric, prospective, observational, cohort study. The ICMR selected five Level I trauma centres (as per the classification given in WHO’s Guidelines for Essential Trauma Care (13)) from different parts of the country to form the national task force to conduct this study. These trauma centres are - Pramukhswami Medical College and Shree Krishna Hospital, Karamsad, Anand (West India), M.S Ramaiah Medical College and Hospital, Bengaluru (South India), Jai Prakash Narayan Apex Trauma Centre, All India Institute of Medical Sciences, New Delhi (North India), King George’s Medical University, Lucknow (North India) and Jubilee Mission Medical College & Research Institute, Thrissur (South India). In addition, two Level II and three Level III hospitals, meeting predefined requirements will be selected from each site. Thus, 30 hospitals (5 level I, 10 level II and 15 level III hospitals) will be involved in this study.

### Phases of the study

#### (I) Preparatory phase

**Administrative support**: Administrative support will be sought from the District Collector, the Superintendent of Police, the District Medical Officer, the Mayor and other functionaries in the city/district. The elected representatives of the city and district will be met to seek their support. A document highlighting the burden of RTIs will be prepared for each site and the same will be used for advocacy efforts.

**Identification and defining the role of partner hospitals (Level II and Level III hospitals)**: The partner hospitals would be identified on the basis of their geographical location and selected purposively at each of the five sites. Each level I hospital will select two level II and three level III hospitals. Once identified the roles and responsibilities of partner hospitals and the nodal officers at each hospital will be defined and given as written protocol.

**Situation analysis**: The situation of the district in terms of the epidemiology of RTIs and trauma care facilities available in the district would be done. The trauma care capacity will be assessed in all the 30 hospitals. Other facilities like EMS and ambulance services available will be listed in the documents. A situational analysis tool based on the WHO’s publication - “Guidelines for Essential Trauma Care” would be used for this purpose (13).

#### (II) Trauma registry establishment and pre-intervention data collection

Establishment of an online electronic registry for data collection would be completed by the end of 4 months of commencement of the project. The pre-intervention data will be collected through the registry in all participating centres. This phase will continue for 6 months. Trained research personnel would ensure data collection with a pre-set proforma in all participating hospitals.

**Trauma registry:** The registry will start functioning from the 5^th^ month of the project. After reviewing the pilot observations, an easy surveillance tool will be prepared for data collection in English, which might be translated for instruction in local languages for easy understanding by the research personnel. A detailed data set would be prepared to enter pre-hospital, in-hospital and post-discharge details of all the admitted patients.

**Data abstraction training:** Training for project personnel would be carried out at the institute of the principal investigator. Data collectors will be sitting in the emergency department of level 1 hospital for 24/7 on shift duties and record patient details into the prescribed registry proforma. In level II and level III centres, the emergency staff will collect data in the registry proforma and will hand over this proforma to the research team as per the agreement signed by these partner hospitals. These data will be transferred into the online registry.

The data management training including training on data dictionary (ICD, AIS), various types of data coding, injury severity scoring and training on other data management tools would also be undertaken for research personnel. This is aimed not only to help in the current project but also to help in capacity building for future trauma registries.

**Data collection:** Registry data collection will be done by research personnel under the supervision of the principal investigator and other senior staff based on the preset registry proforma. The proforma used for trauma registry is appended to this paper as Appendix.

#### (III) Intervention

The intervention phase will last for 6 months and shall include: (a) education of the first responders, (b) prehospital notification training, (c) acute trauma care training and improving the quality of care.

**(a) Education of the first responders:** The intervention in this study is to educate and train the first-responders like ambulance or emergency medical technician personnel, police and fire and safety services staff. The training will include basic education on the initial assessment of a trauma patient in the form of AIIMS Trauma First Responder (TFR) course. The training will be for 6–8 hours for one day conducted once every month for 6 months during the intervention period.

**(b) Prehospital notification training:** The recipient hospital needs to be notified about patient’s basic injuries and vitals while en-route, so that the receiving hospital has enough time to assemble a team, which is ready to receive and treat the patient upon arrival.

Level I trauma hospital will be issued mobile phones, with a dedicated toll-free number as part of the intervention. Panels comprising representatives of trauma hospital and feeding pre-hospital providers would be convened and, locally-tailored protocols and forms for the following made: (i) notification that specifies about whom, to whom and when the notification should be given, and what information should be communicated; (ii) responding at the receiving end, in particular assembling a receiving trauma team for cases requiring immediate resuscitation; (iii) documentation of call details, including the time of call, the information provided, and perceptions of its utility and any care that ensued; and (iv) structured handover upon arrival to the hospital.

**(c) Acute trauma care training and improving the quality of care:** AIIMS Trauma Assessment and Management (ATAM) course will be conducted providing training to the doctors and nurses catering to the RTI victims. ATAM would be held once every month at the level I hospital for a total duration of 6 months during the intervention phase. ATAM is a two-day course, which provides structured training in acute trauma management with special emphasis on skills training. Pre and post-test will be conducted with each course as a part of a quality improvement (QI) programme.

QI activities will be implemented according to the WHO guidelines to become focal points for training in their region. The intervention will include the WHO trauma QI training course for key clinicians and administrators, conducted during the first six months, followed by mentoring of development of the necessary structures and processes to conduct regular mortality and morbidity (M & M) meetings, preventable death reviews, audit filters, risk-adjusted benchmarking of key performance indicators where relevant and loop closure. The trainers and mentors will be drawn from the project leadership team.

#### (IV) Impact evaluation

Post-intervention trauma registry data collection would be carried out for 12 months after the intervention phase. Internal and external quality assurance would be carried out on a monthly basis. As mentioned at every stage of the study, the impact of the intervention will be measured through various outcome indicators, including the patients’ outcome like death, length of stay in hospital, morbidity, disability, etc. The necessary data for an impact evaluation will be obtained through the registry. Both pre- and post-intervention comparisons among various outcome variables will be made.

### Study outcomes

The primary outcome measure will be early preventable mortality, defined as death at 24 hours after admission for patients with a calculated probability of survival >50% based on their injury severity score. Secondary outcomes will be (i) the proportion of patients for whom the notification was indicated who had notification initiated, (ii) the proportion of patients who met criteria for assembly of a receiving trauma team for whom a team was assembled and (iii) ICU and hospital length of stay, etc.

### Data analysis

Quantitative data (continuous variables) will be presented as mean, standard deviation and range (if symmetrically distributed data) or as median and interquartile range (if asymmetrically distributed data). Ordinal and nominal data shall be presented as proportion and percentage. Student’s t-test will be used to compare the difference of means whereas; the Wilcoxon ranked sum test will be used to evaluate the statistical significance of the difference of medians. The Chi-square test or Fisher’s exact test shall be used to compare the difference of proportions (categorical variables). A p value of <0.05 was considered as the minimum level for statistical significance.

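### Ordinal data are pooled with nominal data, which apparently routes any graded impact indicator to an unordered test that ignores grade order (minor, conditional on how disability and morbidity are recorded)

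*Protocol article*

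**What the plan says.** The Data analysis section of the protocol article sorts variables into two groups. Continuous variables get a mean, standard deviation and range if symmetric, or "median and interquartile range (if asymmetrically distributed data"). The other group is everything categorical: "Ordinal and nominal data shall be presented as proportion and percentage".

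Tests are then assigned by type of summary. The t-test goes with means. For medians, "the Wilcoxon ranked sum test will be used to evaluate the statistical significance of the difference of medians". For the rest, "The Chi-square test or Fisher’s exact test shall be used to compare the difference of proportions (categorical variables"). The significance threshold is 0.05. No trend test or ordinal model is listed.

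Outcomes appear in two places. Study outcomes gives the primary outcome as "early preventable mortality, defined as death at 24 hours after admission for patients with a calculated probability of survival >50" per cent, which is binary. The first two secondary outcomes are proportions, for example "the proportion of patients for whom the notification was indicated who had notification initiated", and the third is ICU and hospital length of stay. The section on phase IV, impact evaluation, adds a wider list of indicators: "patients’ outcome like death, length of stay in hospital, morbidity, disability, etc". It gives no scale, number of grades or time point for morbidity or disability.

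**The concern.** The plan names ordinal data as a type it expects and then gives it the same treatment as nominal data. An ordinary chi-square or Fisher's exact test on a table with more than two categories takes no account of their order. It asks whether the two periods differ in any way, not whether patients moved towards better grades. The study asks the second question: whether outcomes improve after the training and notification intervention.

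Two things are at stake for a graded indicator. The unordered test spreads its power over all possible departures, so it is less sensitive to a consistent shift. Its p value also carries no direction: a significant result could reflect improvement, deterioration or a reshuffling of grades.

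**Working it through.** **1. Which test do the stated rules give to ordinal data?** Ordinal data are given proportions and no other summary. Proportions are given chi-square or Fisher. The rank-sum test is given to medians, and medians only to asymmetric continuous data. Following the rules, the unordered tests are the only route. This is inferred from three sentences read together; none names a test for ordinal data.

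**2. Which outcomes could be affected?** 24-hour death and the two notification and trauma-team proportions are binary. Length of stay is quantitative. None is ordinal. That leaves morbidity and disability from the impact-evaluation list, if graded.

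**3. Does the test ignore order?** For an illustrative five-grade table (pre 150/60/36/24/30, post 360/110/60/35/35), chi-square = 10.813, p = 0.0287. After shuffling the columns it is again 10.813, p = 0.0287.

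**4. Size.** The article states no power, effect size, distribution or sample size, so there is no figure to reproduce. Assumptions:
- Two-sided alpha of 0.05 (sidedness is not stated).
- 1:2 pre:post allocation, from 6 and 12 months of data at constant accrual.
- Independent patients.
- A proportional-odds shift with odds ratio 1.2 to 1.5.
- Enough patients for the rank-sum test to have 80% power.

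With grade probabilities p (pre) and q (post), pooled probabilities m and midrank scores r:
- Pearson noncentrality = n1 Σ(p − m)²/m + n2 Σ(q − m)²/m, on k − 1 degrees of freedom.
- Rank-sum noncentrality = [Σ(q − p)r]² / [Var(r)(1/n1 + 1/n2)], on 1 degree of freedom.

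Example with five grades, p = 0.50/0.20/0.12/0.08/0.10, odds ratio 1.5, n1 = 259 and n2 = 518. Then q ≈ 0.600/0.178/0.095/0.059/0.069, the difference in mean score is 0.05547 and Var(r) = 0.06748. The rank-sum noncentrality is 0.05547² / [0.06748 × (1/259 + 1/518)] = 7.87, and the Pearson noncentrality is 7.88. The two are nearly equal, but Pearson spends its value on 4 degrees of freedom. Power is 80% for rank-sum and 60% for chi-square. A simulation of 3,000 trials gave 78.5% and 60.5%.

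Because the noncentralities nearly coincide under proportional odds, the loss depends almost only on the number of grades. The rank-sum test needs 7.849 for 80% power:

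| Grades | df | Chi-square power at 7.849 | Noncentrality for 80% | Ratio to 7.849 |
|---|---|---|---|---|
| 2 | 1 | 80% | 7.849 | 1.00 |
| 3 | 2 | 71% | 9.635 | 1.23 |
| 4 | 3 | 65% (64.5%) | 10.903 | 1.39 |
| 5 | 4 | 60% | 11.935 | 1.52 |
| 7 | 6 | 52% | 13.624 | 1.74 |

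The ratio is the factor by which patient numbers would have to rise to recover 80%. The results were almost the same for odds ratios 1.2, 1.3 and 1.5, and for flat and skewed five-grade distributions.

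**5. A case that goes the other way.** Suppose the grades spread to both extremes: p as in the example, q = 0.54/0.14/0.12/0.06/0.14, with 300 and 600 patients. The Pearson noncentrality is 8.83 and the rank-sum noncentrality 0.08, giving power of 65% and 6%.

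**The case against.** The strongest reply is that the article commits no identified outcome to an unordered test. The sentence on ordinal data concerns presentation, and showing ordinal data as percentages is good practice. The article gives no scale for disability; it may be a yes/no item in the registry proforma, which the article appends and which is not at hand. Matching a test to each scale is often left to a fuller document. Chi-square on an ordered table also keeps its type I error, so the issue is efficiency, not validity. The power comparison uses the alternative that most favours the rank-sum test.

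Most of this stands, and it limits the point. It does not remove it. The section does more than stay silent: it names ordinal data, pools it with nominal data and lists tests by summary type, leaving only one route. That is a stated rule, and a better one is available within the same section.

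A reader might infer that the study's main comparisons are underpowered. The documents do not support this: the primary and named secondary outcomes are not ordinal, and without a sample size no actual power can be computed. A reader might also infer that direction would be lost altogether. It would not, because the per-grade percentages before and after still show it descriptively; only the test lacks it.

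**Conclusion.** The point holds as a minor, conditional one. As written, the Data analysis section apparently sends ordinal outcomes to tests that ignore grade order. It matters only for morbidity and disability, and only if they have three or more ordered grades.

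In that case, and under a consistent shift, the unordered test gives up about 9, 15 or 20 points of power from 80% with 3, 4 or 5 grades, equal to needing about 23%, 39% or 52% more patients. These figures rest on the assumed proportional-odds shift, 1:2 allocation, two-sided alpha and independent patients. There is no loss for a binary indicator, and the advantage reverses for a change towards both extremes. It would go too far to say that the plan prescribes chi-square for disability, or that a loss of power has been shown for this study.

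**What to change.** In Data analysis, separate ordinal from nominal data. State that any graded outcome will be compared pre versus post with the rank-sum test already listed, corrected for ties, or with a proportional-odds model reporting a common odds ratio and 95% confidence interval. Keep chi-square or Fisher's exact test for binary and nominal variables, and keep per-grade percentages as the descriptive table. Stating the scale on which disability and morbidity are recorded would settle whether the rule applies to them.

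The cost is about one sentence, with no new data or patients. The downside is lower sensitivity to non-monotone changes and, for the model, reliance on proportional odds. The per-grade table lets readers check both.

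### Student's t-test is named for means, yet pre- and post-intervention periods of 6 and 12 months make it sensitive to unequal spread; Welch's test would remove that dependence

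*Protocol article*

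**What the plan says.** The Data analysis section of the protocol article sorts continuous variables by shape. Symmetric ones are summarised by means and asymmetric ones by medians. It then says that Student's "t-test will be used to compare the difference of means whereas" the Wilcoxon rank-sum test serves for medians. Proportions go to the chi-square or Fisher's exact test. The threshold is: "A p value of <0.05 was considered as the minimum level for statistical significance". No unequal-variance form of the t-test is mentioned, and symmetry is the only condition for the route that leads to it.

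The collection periods differ in length. On the pre-intervention period, phase II states: "This phase will continue for 6 months". On the later period, phase IV states: "Post-intervention trauma registry data collection would be carried out for 12 months after the intervention phase". The registry is to "enter pre-hospital, in-hospital and post-discharge details of all the admitted patients", and the same impact evaluation section announces the comparison: "Both pre- and post-intervention comparisons among various outcome variables will be made".

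The only continuous outcome named in Study outcomes is "ICU and hospital length of stay". The primary outcome (death at 24 hours among patients with a calculated survival probability above 50%) and the notification and team-assembly outcomes are proportions.

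**The concern.** Student's two-sample t-test estimates one common variance from both groups. In large samples this does no harm when the groups are of equal size, because the pooled standard error is then correct even if the spreads differ. With unequal sizes that protection is lost. The larger group dominates the pooled variance, while the smaller group contributes most to the true variance of the difference in means. If the smaller group is the more variable, the standard error is too small and false positives rise. If it is the less variable, the standard error is too large and power falls.

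The design makes unequal groups likely, and symmetry of a distribution says nothing about equality of spread. At stake are the p values and confidence intervals for those registry variables that are treated as symmetric and compared between periods.

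**Working it through.** **Inputs from the protocol article**
- Significance level 0.05 (Data analysis). Sidedness is not stated; two-sided is assumed.
- Pre-intervention collection 6 months (Abstract, phase II); post-intervention collection 12 months (phase IV).

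**Assumptions, because the article gives no patient numbers and no SDs**
- k = n_post / n_pre = 12/6 = 2, which holds if admissions are steady. Values of 1, 1.5 and 3 are also shown.
- r = SD_pre / SD_post, from 0.5 to 2.

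**Formulas (large samples; both variances in units of SD_post² / n_pre)**
- True variance of the difference in means: r² + 1/k
- Variance that the pooled test uses: [(r² + k)/(1 + k)] × (1 + 1/k). At k = 2 this is (r² + 2)/2.
- True two-sided level: 2[1 − Φ(1.96 × √(pooled/true))]

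**Reproducing the stated level.** At r = 1 and k = 2, true = 1.5 and pooled = 1.5, so the level is 5.0%, as the plan intends.

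**Unequal spread at k = 2**
- r = 1.5: true = 2.25 + 0.5 = 2.75; pooled = 4.25/2 = 2.125; 1.96 × √(2.125/2.75) = 1.72; level 8.5%.
- r = 1/1.5: true = 0.444 + 0.5 = 0.944; pooled = 2.444/2 = 1.222; 1.96 × √(1.222/0.944) = 2.23; level 2.6%.
- r = 0.9: true = 1.31; pooled = 1.405; level 4.2%.
- r = 1.1: true = 1.71; pooled = 1.605; level 5.8%.

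**Dependence on the patient ratio (true level of the pooled test)**

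| n_post : n_pre | r = 0.5 | r = 0.667 | r = 1 | r = 1.5 | r = 2 |
|---|---|---|---|---|---|
| 1 | 5.0% | 5.0% | 5.0% | 5.0% | 5.0% |
| 1.5 | 2.7% | 3.4% | 5.0% | 7.0% | 8.2% |
| 2 | 1.6% | 2.6% | 5.0% | 8.5% | 11.0% |
| 3 | 0.8% | 1.7% | 5.0% | 10.7% | 15.0% |

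The first row shows that unequal spread alone does no damage; it must be combined with unequal group sizes. The sample size cancels out of the formula, so more patients do not help.

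**Simulation (independent normal data, 20,000 runs per setting, 1:2)**

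| r | Student, 50 vs 100 | Student, 500 vs 1000 | Welch, 50 vs 100 | Welch, 500 vs 1000 |
|---|---|---|---|---|
| 0.667 | 2.8% | 2.6% | 5.0% | 4.9% |
| 1 | 4.7% | 4.9% | 4.8% | 4.9% |
| 1.5 | 8.4% | 8.8% | 5.0% | 5.2% |
| 2 | 10.9% | 11.2% | 4.7% | 4.9% |

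Over all settings with r from 0.5 to 2, Welch's test stayed between 4.7% and 5.2%.

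**The case against.** The strongest reply is that no named outcome is shown to be affected. The primary outcome and two of the named secondary outcomes are proportions. Length of stay is the one continuous outcome, and if it is skewed the article already sends it to the rank-sum test. This stands, and it keeps the point small.

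A second reply is that the article never says that variances are pooled, that authors use the name Student's t-test loosely, and that a fuller analysis plan may already specify Welch's test. The first part is true of the wording. But the article does name a test, and the ordinary meaning of that name is the equal-variance form. Asking for a better-suited named test is therefore different from asking for missing detail.

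Some stronger readings are tempting and are not supported:
- A reader might infer that equal spread is implausible, because the Discussion mentions government schemes that could bring patients with minor injuries to level I centres. That passage concerns case mix as a competing explanation. It says nothing about the variance of any variable, and a changed mix could widen or narrow the later spread.
- A reader might infer an excess of false positives. The direction is unknown, and the test could equally be conservative.
- A reader might take 1:2 as fixed by the plan. The plan fixes months, not patients.
- A reader might regard the rank-sum route as safe. That test is also sensitive to unequal spread, and changing the t-test does not alter this.

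**Conclusion.** The point holds in conditional form and is a free improvement, not a flaw in the main analysis. If group sizes are near 1:2 and the spread of a variable differs between periods, the named test does not keep its 5% level at any sample size. It gives about 8.5% or 2.6% for an SD ratio of 1.5 in one direction or the other. With SDs within about 10% of each other, the departure (4.2% to 5.8%) is too small to matter.

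The conclusion rests on the usual equal-variance meaning of Student's t-test, steady admissions, a two-sided test, and SD ratios that the documents neither give nor exclude. It reaches only unpaired comparisons of means between pre- and post-intervention patients. The documents do not show that any particular result would be wrong.

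**What to change.** In the Data analysis section, replace Student's t-test with Welch's unequal-variance t-test for unpaired comparisons of means between pre- and post-intervention patients, and report the mean difference with its Welch 95% confidence interval. Limit the change to those comparisons. The pre- and post-test scores from the training course in phase III come from the same trainees, so they are paired and need a paired method.

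The cost is a change of wording. No extra patients or data are needed, and the loss of power when spreads are equal is negligible. Welch's test still treats patients as independent. It does not deal with clustering in 30 hospitals at five sites, nor with confounding between periods, which the Discussion acknowledges. Its simulated 5% level should not be read as a guarantee for these data.
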